### Objectives {7}

Based on the potential benefits from reducing cumulative prednisolone dose and the possible positive effects of active vitamin D in nephrotic syndrome, the study will test the following hypothesis:
Treatment of MCN with a reduced dose of prednisolone in combination with active vitamin D is non-inferior to standard dose of prednisolone with respect to rate and time to remission.Treatment of MCN with a reduced dose of prednisolone in combination with active vitamin D reduces the incidence of both the observed and subjective adverse events compared with the standard dose of prednisolone.Patients with MCN and a fast turnover of prednisolone have a lower rate of remission, longer time to remission, and fewer adverse events than patients with a slow turnover of prednisolone.

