#### Criteria for discontinuing or modifying allocated interventions {11b}

Prednisolone dose in both arms as well as alfacalcidol dose in the experimental arm may be reduced or discontinued if patients develop severe adverse events to these drugs as assessed by the local investigator. If possible, any deviation from the dosing regimen should be discussed with the sponsor prior to modification. Examples of severe adverse events are hypercalcaemia due to alfacalcidol treatment or psychoses, osteoporotic fracture, development of diabetes, or severe infections during high-dose prednisolone treatment.

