### Outcomes {12}

Remission is defined by a urine-protein/creatinine ratio < 0.4 g/g and/or a urine-albumin/creatinine ratio < 0.3 g/g on two consecutive tests.

Relapse is defined as the recurrence of proteinuria, i.e. a urine-protein/creatinine ratio > 0.75 g/g and/or urine-albumin/creatinine ratio > 0.5 g/g in two consecutive tests and a decline in p-albumin of > 3 g/l.

Primary endpoints:
Rate of remissions after 16 weeks.Time from diagnosis to remission.

Secondary endpoints:
Rate of relapse within 1 year after remission.Time from remission to relapse.Rate of adverse events and number of hospital admissions.The associations between genetic variations in liver enzyme genes, the concentration of prednisolone in saliva, and remission or relapse.

Safety endpoints:
Patient survivalAcute kidney injury (AKI stage 2 or 3 as defined by KDIGO [31])Serious infections requiring admissionPersistent hypercalcaemia (> 2 weeks) defined by an elevated plasma-ionised-calcium and not normalising by reducing alfacalcidol dose.Severe adverse effects to prednisolone, e.g. gastrointestinal bleeding and severe depression

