### Assignment of interventions: blinding

#### Who will be blinded {17a}

The study is an open-label study, and neither the patients nor the investigators will be blinded to the interventions. Baseline data are collected independent of randomisation as it is collected prior to this.

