### Adverse event reporting and harms {22}

Subjective events during the trial will be reported by patients in questionnaires (SF36 and Cushing QoL). Local investigators will report adverse events after results of blood test (development of diabetes, infections, hyperlipidaemia), examinations (hypertension, weight gain, skin toxicity), and questionnaires (glucocorticoid toxicity index). All the events will be collected and stored in RedCap. In case of severe adverse events, the sponsor will be informed and report it to relevant authorities.

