## Discussion

Lower dose of prednisolone in combination with active vitamin D in MCN might be an applicable option for sufficient disease control as a few small randomised studies suggest [14, 32–34].

Patients with MCN and nephrotic syndrome often have no co-morbidities. When being diagnosed with MCN, they experience symptoms such as oedema, fatigue, and foaming urine. After initiating medical treatment, they often experience additional changes and events, which can be related to both the disease and the treatment strategy. Is it imperative that we trace a treatment strategy that is minimising treatment-related adverse events.

This trial uses a predefined electronic randomisation open-labelled design. The open-label design reflects the daily clinically reality. Adherence to treatment strategy and patient compliance will be monitored, e.g. by counting pills. It is commonly anticipated that lower dose of prednisolone decreases adverse events. This might encourage a speedy reduction of prednisolone dose or cross-over from standard to reduced dose of prednisolone especially if the patient prior to treatment has obstacles with e.g. obesity, osteoporosis, hypertension or other known adverse events to prednisolone treatment. Local investigators will be encouraged to adhere to treatment strategy and change in prednisolone dose can only be done after agreement with sponsor or his substitute. The trial will provide evidence to the commonly anticipated belief that the number of adverse events increases with the dose of prednisolone. Alfacalcidol is a well-known treatment among nephrologists and widely used in other patients with chronic nephropathies. Using it in patients with MCN is newfound but expected to be tolerable.

Self-reported, prednisolone associated adverse events have not been systematically evaluated in MCN, but in renal transplant patients, the cumulative dose of prednisolone correlates with reported adverse effects using the Cushing QoL questionnaire [26, 27] and SF36 [35].

This trial should allow us to determine if low dose prednisolone in combination with active vitamin D is clinically as efficient as current standard therapy to induce remission in MCN with the potential to reduce significant adverse events. This may lead to changes of current guidelines for the treatment of MCN. If so, the results potentially can inspire to additional trials in other prednisolone-treated diseases to examine reduced dose of prednisolone.

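### One safety endpoint counts severe events only once they are attributed to prednisolone, from an open-ended list, in an open-label trial of prednisolone dose

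*Protocol article*

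**What the plan says.** All references are to the protocol article.

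- **Outcomes {12}**, last safety bullet: "Severe adverse effects to prednisolone, e.g. gastrointestinal bleeding and severe depression". It gives no criterion for severity and names no assessor.
- **Who will be blinded {17a}**: "neither the patients nor the investigators will be blinded to the interventions".
- **Adverse event reporting and harms {22}**: "Local investigators will report adverse events after results of blood test", and also after examinations and questionnaires.
- **Discussion**: "It is commonly anticipated that lower dose of prednisolone decreases adverse events". The Discussion paragraph of the Abstract likewise expects a lower dose to mean fewer severe events.
- **Criteria for discontinuing or modifying allocated interventions {11b}**: study drug may be changed "if patients develop severe adverse events to these drugs as assessed by the local investigator". The prednisolone examples given there are "psychoses, osteoporotic fracture, development of diabetes, or severe infections during high-dose prednisolone treatment".
- **Objectives {7}**, second hypothesis: the reduced regimen "reduces the incidence of both the observed and subjective adverse events compared with the standard dose of prednisolone".

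**The concern.** An adverse effect of a drug is an event plus a causal judgement. Here the judgement concerns the drug whose dose is randomised, and nothing in the article hides the dose from those who report events. A person who expects the higher dose to cause more harm may blame prednisolone for a bleed or a depressive episode more readily at 1 mg/kg/day than at 0.5 mg/kg/day. The endpoint would then favour the reduced arm even if the same number of bleeds and depressions occurred in both.

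The open list adds a second choice: whether an unnamed event, such as a fracture or new diabetes, belongs to the category at all. Both choices can lean the same way, towards the result that the second hypothesis predicts.

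Most of the neighbouring safety bullets show that a firmer definition was within reach. Survival, acute kidney injury by KDIGO stage and infections requiring admission do not depend on attribution to prednisolone.

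**Working it through.** The article gives no event rate and no attribution rate for this endpoint, so there is no figure to reproduce. The check is first textual, then an illustration under stated assumptions.

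**1. Does counting require attribution?** Yes. The bullet is worded as effects of prednisolone, not as events during treatment. By contrast, the secondary endpoint on adverse events and hospital admissions in the same section carries no such wording.

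**2. Who attributes?** The bullet does not say. Section {11b} gives the local investigator the assessment of drug-related severe events, but for changing study drug. Section {22} has local investigators report adverse events. Section {17a} says they are not blinded. An unblinded attributor is a reasonable inference from these three sections, not a stated rule.

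**3. Is the content of the category fixed?** No. The bullet's two examples (gastrointestinal bleeding, severe depression) share no item with the four prednisolone examples in {11b} (psychosis, osteoporotic fracture, diabetes, severe infection). Taking the two sections as a whole, there is overlap: hypercalcaemia and serious infection appear in {11b} and also as separate safety endpoints in {12}.

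**4. What could unequal attribution do?** Assume the same true risk r in both arms, with attribution probability aS in the standard arm and aR in the reduced arm.

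- Observed risks: pS = r × aS and pR = r × aR.
- Expected false risk ratio: pR/pS = aR/aS, whatever r is.
- Chance of a falsely significant result favouring the reduced dose (two-sided 0.05, normal approximation, n per arm, p̄ the mean of pS and pR): Φ{[(pS − pR) − 1.96 √(2p̄(1 − p̄)/n)] / √[(pS(1 − pS) + pR(1 − pR))/n]}.

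Input from the article: n = 43 completers per arm (Sample size {14}). Assumed: r, aS and aR.

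Worked case, r = 20%, aS = 0.8, aR = 0.6:

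- pS = 0.16, pR = 0.12, p̄ = 0.14.
- Null standard error = √(2 × 0.14 × 0.86/43) = 0.0748.
- Alternative standard error = √[(0.1344 + 0.1056)/43] = 0.0747.
- (0.04 − 1.96 × 0.0748)/0.0747 = −1.43, and Φ(−1.43) is about 0.077.

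| r, both arms | aS v aR | Observed risk | Expected count of 43 | Risk ratio | Falsely significant for reduced dose |
|---|---|---|---|---|---|
| any | 0.8 v 0.8 | equal | equal | 1.00 | 2.5% (nominal) |
| 10% | 0.8 v 0.6 | 8% v 6% | 3.4 v 2.6 | 0.75 | 5.5% |
| 20% | 0.8 v 0.6 | 16% v 12% | 6.9 v 5.2 | 0.75 | 7.7% |
| 40% | 0.8 v 0.6 | 32% v 24% | 13.8 v 10.3 | 0.75 | 12.7% |
| 10% | 0.8 v 0.4 | 8% v 4% | 3.4 v 1.7 | 0.50 | 11.8% |
| 20% | 0.8 v 0.4 | 16% v 8% | 6.9 v 3.4 | 0.50 | 20.5% |
| 40% | 0.8 v 0.4 | 32% v 16% | 13.8 v 6.9 | 0.50 | 41.0% |

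A milder gap of 0.7 v 0.6 gives a ratio of 0.6/0.7 = 0.86. With counts this small the normal approximation is rough, so the last column shows direction and order of size only.

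**The case against.** Five points can be made on the other side.

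- **The adverse event hypothesis does not rest on this bullet.** It concerns observed and subjective events. The article also collects the overall adverse event rate, admissions, the Glucocorticoid Toxicity Index, SF36 and Cushing QoL. This stands, and it limits the point to one safety endpoint. Those measures are also collected open-label, so they do not cure the definition, but they are not defined by it.
- **No assessor is named.** A reader might infer that the plan lays down attribution by an unblinded local investigator. The article does not say so for this endpoint, and adjudication may be described in the full protocol, which is not shown. This stands as a limit on what can be claimed. The attribution wording itself remains.
- **The two example lists do not contradict each other.** A reader might infer a conflict, or that fracture and diabetes are left out of the endpoint. Neither follows. Both lists are offered as examples and serve different purposes: one illustrates an endpoint, the other gives grounds on which "Prednisolone dose in both arms as well as alfacalcidol dose in the experimental arm may be reduced or discontinued". New diabetes is also reported as an adverse event under {22}. What survives is that the category has no fixed content.
- **The reference to high-dose treatment in {11b} might be read as confining those examples to the standard arm.** The same section opens by covering prednisolone in both arms, so that reading fails.
- **The illustration returns what is put into it.** This is true: the ratio is the assumed attribution ratio. It shows the mechanism, not its size. Statistical methods {20a} also names no confirmatory test for safety endpoints, so the false-significance column describes how a result might be read, not a planned decision.

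**Conclusion.** The point holds in a limited form. As written, the endpoint needs a causal judgement about the randomised drug, has an open event list, and sits in an open-label trial whose article records the expectation that favours the reduced arm. Followed as written, it can show fewer prednisolone effects in that arm without any true difference.

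The size is unknown. Under the assumed attribution gaps the false risk ratio runs from 0.86 (0.7 v 0.6) through 0.75 (0.8 v 0.6) to 0.50 (0.8 v 0.4), and it is 1.00 if attribution is equal. The conclusion assumes that whoever attributes events knows the arm. The text makes this likely but does not state it. The article does not support a claim that the whole adverse event comparison is compromised. The endpoint is not primary, but the change is cheap and worth making before the arms are compared.

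**What to change.** In Outcomes {12}, replace the bullet with a closed list of severe events built from the article's own terms: gastrointestinal bleeding, severe depression, psychosis, osteoporotic fracture and new-onset diabetes. Serious infection already has its own endpoint and need not be repeated. Give each event an objective criterion, such as an admission, an imaging report or a laboratory threshold. Count every event that meets its criterion, identically in both arms and whatever the attributed cause. Record the investigator's causality opinion as a descriptive field only.

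Leave the treatment-modification rule in {11b} as it is. Ask only that its examples of severe prednisolone events and those in {12} be reconciled, so that a reader knows how the two relate.

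The cost is protocol wording and a few eCRF fields. Recruitment has started, so events already entered in RedCap would have to be checked against the list. The statistical downside is a little noise: events unrelated to prednisolone will be counted in both arms, which pulls a true risk ratio somewhat towards 1.

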### Participant timeline {13}

See Fig. 1.

**Fig. 1 Fig1:**
[figure not shown]
Participant timeline

### Sample size {14}

Based on current data, 80% of patients are expected to achieve remission after 16 weeks of standard treatment [8]. It is considered clinically significant if the remission rate in the low prednisolone + alfacalcidol regimen is less than 90% of the standard treatment regime. Using a non-inferior design with 80% power and a P value of = 0.05, we estimate that 43 patients in each group would need to complete the study. To allow for withdrawals, the study will recruit 96 patients. The incidence of adult MCN in Denmark is 7.3/m/year [4], and with all Danish renal departments participating in the trial, the inclusion is expected to be completed within 4 to 5 years.

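### 43 patients per group do not give 80% power for a margin of 90% of an 80% remission rate; with equal true rates the power is about 25%

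*Protocol article*

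**What the plan says.** The Sample size section {14} of the protocol article gives these inputs and one result:

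- Control rate: "80% of patients are expected to achieve remission after 16 weeks of standard treatment".
- Margin: it is considered clinically significant if "the remission rate in the low prednisolone + alfacalcidol regimen is less than 90% of the standard treatment regime".
- Design, error rates and result: "Using a non-inferior design with 80% power and a P value of = 0.05, we estimate that 43 patients in each group" must complete. Whether the 0.05 is one- or two-sided is not said.
- Recruitment is set at 96 to allow for withdrawals.

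No expected remission rate is given for the reduced-dose arm. Objectives {7} puts non-inferiority for rate of and time to remission as the first hypothesis, and the Background describes the new regimen as equally efficient. Outcomes {12} lists remission after 16 weeks as a primary endpoint. The Discussion says: "This trial should allow us to determine if low dose prednisolone in combination with active vitamin D is clinically as efficient" as current standard therapy, and that guidelines may change as a result.

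**The concern.** A margin of 8 points around an 80% rate normally needs several hundred patients per arm, so 43 stands out at once. All the figures are in one paragraph, and the result should follow from them.

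At stake is the power for the main hypothesis. If it is far below 80%, the trial will most likely end inconclusive even when the two regimens are identical. The practical risk is that a non-significant difference is then taken as evidence of equal efficacy, although a loss well beyond the protocol's own limit would still be compatible with the data. The protocol does not propose that reading, but the confidence of the Discussion invites it. No interim analysis is planned (Interim analyses {21b}) that could expose the shortfall earlier.

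**Working it through.** **Inputs**

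- Control remission rate 0.80; margin ratio 0.90, so 0.90 × 0.80 = 0.72, a difference of 0.08; power 0.80; 43 completers per group; 96 recruited (all from Sample size {14}).
- 1:1 allocation (Sequence generation {16a}), so 48 recruited per group.
- Assumption: true reduced-dose rate 0.80, because the hypothesis is equal efficacy and no other rate is stated.
- Alpha: both readings are tried, one-sided 0.05 (z = 1.645) and one-sided 0.025 (z = 1.960). For 80% power, z = 0.842. The squared sums are 2.487² = 6.183 and 2.802² = 7.849.

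**Attempt to reproduce 43**

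*Difference scale:* n = (z sum)² × 2 × 0.8 × 0.2 / 0.08²
- one-sided 5%: 6.183 × 0.32 / 0.0064 = 309.1, so 310
- one-sided 2.5%: 7.849 × 0.32 / 0.0064 = 392.4, so 393

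*Log-ratio scale:* n = (z sum)² × 2 × (0.2/0.8) / (ln 0.9)²
- 6.183 × 0.5 / 0.01110 gives 279; at one-sided 2.5%, 354

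*Linear contrast (reduced rate minus 0.9 × standard rate):* variance term 0.16 × (1 + 0.81) = 0.2896
- 280; at one-sided 2.5%, 356

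Other readings also fail:

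| Reading | n per group |
|---|---|
| 10 absolute points, not 8 | 198 (one-sided 5%) or 252 (one-sided 2.5%) |
| Superiority, 80% vs 72% | 352 to 471 |
| Superiority, 80% vs 90% | 157 to 219 |
| One-sample test | 99 to 197 |

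Treating 0.90 as a hazard-ratio limit for time to remission would need 2,228 events at one-sided 5%. The figure of 43 is not reproduced.

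**Power with 43 per group, equal true rates of 80%**

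The standard error of the difference is √(0.32/43) = 0.0863.

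| Scale | one-sided 5% | one-sided 2.5% |
|---|---|---|
| Difference, 8 points: Φ(0.08/0.0863 − z) | 23.7% | 15.1% |
| Log ratio, 0.90: Φ(0.1054/0.1078 − z) | 25.2% | 16.3% |
| Exact enumeration, difference (Wald bound) | 24.6% | 16.0% |
| Exact enumeration, log ratio (Wald bound) | 26.4% | 17.2% |

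With all 48 per group and no withdrawals, the normal approximation gives 25.3% and 27.0% at one-sided 5%, or 16.4% and 17.7% at one-sided 2.5%.

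**What 43 per group would support**

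- Margin with 80% power at equal rates: 2.487 × 0.0863 = 0.214, about 21 points (59% against 80%); at one-sided 2.5%, 2.802 × 0.0863 = 0.242, about 24 points.
- Keeping the stated margin, a truly better reduced-dose arm. At 90% true remission and one-sided 5%, the difference scale needs 6.183 × (0.16 + 0.09) / 0.18² = 47.7, so 48. The linear contrast needs 6.183 × (0.09 + 0.81 × 0.16) / 0.18² = 41.9, so 42. The log ratio needs 6.183 × (0.1/0.9 + 0.2/0.8) / (ln 1.25)² = 44.8, so 45. At one-sided 2.5% the three scales need 54 to 61.

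**What the data would have to show**

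- If 80% remission is observed in both arms, the lower bound of the difference is −1.645 × 0.0863 = −14.2 points, or −1.960 × 0.0863 = −16.9 points at one-sided 2.5%. Losses up to that size could not be excluded.
- To clear −8 points, the reduced-dose arm must be observed better by about 14.2 − 8 = 6.2 points (16.9 − 8 = 8.9 at one-sided 2.5%). This fixes the standard error at its 80%/80% value. In counts, with 33 to 36 remissions among 43 on standard treatment, it is two or three more remissions on the reduced dose, or three or four at one-sided 2.5%.

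**The case against.** The strongest defence is that the calculation assumed a better result on the reduced dose. The Background argues that active vitamin D may add to the effect of prednisolone, and a true rate of 90% with a ratio margin at one-sided 5% needs 42 to 45 per group, which brackets 43. That may be where the number came from. But the article states no such rate, its hypothesis is equal efficacy, and the explanation fails at one-sided 2.5%. What stands is that the 25% figure is conditional on equal true rates and one-sided 5%, and must be quoted with those conditions.

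A second objection is that the margin, the assumed rate or the sample size could be the misreported item, so the sponsor should look up the original calculation before correcting anything. That is fair and is taken into the fix.

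Third, the sidedness of alpha and the confidence-bound rule are often left to the analysis plan, and this is a condensed article. Agreed: their absence is not counted as an error here. No unseen document, however, can make 43 follow from the inputs printed beside it.

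Finally, correcting the text without adding patients does not repair the design. That is true. Recruitment: Sample size {14} expects 96 patients, hence 86 completers, in 4 to 5 years. Even the smallest requirement, 2 × 279 = 558 completers, is 558/86 = 6.5 times as many, or 26 to 32 years at that pace. Adding Scandinavian sites, as Recruitment {15} allows, is unlikely to close a gap of that size.

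**Conclusion.** The sample-size statement is wrong as written. The stated 43 per group is 6.5 to 9 times too small for the stated margin (279/43 = 6.5; 393/43 = 9.1), and 4.6 times too small even if the margin is read as 10 absolute points at one-sided 5% (198/43). Assuming 80% true remission in both arms, power is about 25% at one-sided 5% and about 16% at one-sided 2.5%, against the 80% claimed. The conclusion does not depend on the sidedness of alpha or on the scale of the margin. It would change only under an unstated assumption that the reduced-dose regimen is clearly superior. If the regimens are equally effective, the trial fails to show non-inferiority about three times in four.

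**What to change.** First recover the original calculation. If it assumed a reduced-dose rate above 80%, state that rate, its justification, the alpha and the scale, and report the power under equal rates beside it.

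If no justified inputs lead to 43, correct Sample size {14} at the present enrolment:

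- Give alpha as one-sided, with its value.
- State that, with 80% remission in both arms, 43 completers per group give about 25% power for the 0.90 ratio margin at one-sided 5% (about 16% at one-sided 2.5%), and 80% power only for a difference of about 21 points (24 at one-sided 2.5%). The second figure describes what the number supports; it is not a proposal to widen the margin.
- Add the decision rule: non-inferiority is claimed only if the lower confidence bound of the remission ratio (reduced over standard) exceeds 0.90. Otherwise the result is reported as an estimate with its confidence interval and called inconclusive.
- In the Discussion, replace the claim that the trial should settle equal efficacy with one that it will estimate the difference, with limited precision.

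The cost is rewording and a much less favourable power statement. No extra patients are needed, but the low power remains and should be acknowledged openly.
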